#### **8.4.5.6 Tissue Samples for Biomarker Analyses**

At the trial site, 1x6 mm lesional biopsies will be collected and split into two equal halves immediately upon sampling at baseline, trial Week 3 and 15. Both parts will be cryopreserved for immunohistochemical, histopathological and gene expression analyses. A non-lesional biopsy (1x3

mm) will also be collected, at baseline only, and cryo preserved for immunohistochemical and histopathological assessments.

The samples will be transferred to screw cap cryotubes and stored frozen (-80°C or below) until shipment to the central laboratory. At the local/central laboratory, samples will be stored frozen (-80°C or below) until shipment. All shipments will be on dry ice.

Labelling of tubes for tissue samples will include the following information:

- Sample type, i.e. “Tissue histo L”, “Tissue histo NL”, “Tissue immuno L”, “Tissue immuno NL”, or “Tissue gene expression”
- Trial ID
- Visit No.
- Subject ID

Tissue samples will be subjected to histopathological, immunohistochemical, and microarray analyses, respectively:

- Histopathological assessments will be conducted at NN referral laboratory
- Immunohistochemical assessments will be conducted at NN referral laboratory
- Microarray analyses will be conducted at Novo Nordisk A/S

#### **8.4.6 PK/PD modelling**

In addition to the non-compartmental (NCA) PK evaluation, a population PK/PD model will be developed (see [17.5](#) for more details).

#### **8.5 Subject compliance**

The trial products (active drug or placebo) will be injected subcutaneously in the abdomen by qualified site personnel, who must be trial independent in order to keep the blinding. Furthermore, within an hour before administration, a trial independent pharmacist or corresponding must prepare the syringes with either placebo or active trial product.

## 9 Trial supplies

### 9.1 Trial products

The following trial products will be supplied by Novo Nordisk A/S:

- Anti-IL-20 (109-0012) 100 mg/vial as sterile freeze-dried powder in single use vials containing 127.5 mg drug substance. One 9 mL powder-containing vial is to be reconstituted with 1.1 mL of sterile Water for Injection, in order to obtain a concentration of 100 mg/mL.
- Placebo solution (Placebo (109-0012) 0 mg/mL) in single use vials containing 9 mL.
- Diluent solution (Placebo (109-0012) 0 mg/mL) in single use vials containing 9 mL to be used for preparation of single use vials of 10 mg/mL and 1 mg/mL strength solutions of 109-0012 for the dose-escalation phases.

The reconstituted Anti-IL-20 (109-0012) 100 mg/vial, as well as the Placebo (109-0012) 0 mg/mL, are colourless/almost clear solutions with pH of 6.5. It is recommended to use the trial drug immediately following reconstitution. The reconstituted preparations should be transferred to the dosing syringe no earlier than 1 hour prior to trial drug administration and stored below 25 °C (no freezing).

Detailed instructions regarding reconstitutions and dilution will be given in the Trial Materials Manual (TMM).

Appropriate volumes of Anti-IL-20 (109-0012) 100 mg/vial or Placebo (109-0012) 0 mg/mL will be administered, based on weight, as subcutaneous injections into the abdomen using a proper syringe. Please see the TMM for details.

The trial products are produced according to Good Manufacturing Practice. A TMM, detailing instructions on storage, handling and administration of the trial products, will be provided by Novo Nordisk. No trial product may be dispensed to any person except to the subjects enrolled into the trial.

### 9.2 Packaging and labelling of trial products

Novo Nordisk A/S will label and pack the trial products.

Trial product will be packed in non subject specific boxes with a unique Dispensing Unit Number (DUN), the DUN of each individual vial contained in a box is identical to the box DUN. The IVRS

will allocate the DUN number(s) to be used for each subject in the MD dose-escalation and MD expansion phase.

Labelling will be in accordance with local law and trial requirements.

### **9.3 Storage and drug accountability of trial products**

The trial products must be stored in a secure place under refrigeration at 2-8°C until use and is stable until the expiry date. The investigator must ensure the availability of proper storage conditions and record and evaluate the temperature. Calibration of the temperature monitoring unit must be done at least once a year. Preferably the temperature must be recorded by continuous, automatic, stationary equipment. It should be placed in the immediate vicinity of trial product. If the equipment does not record the temperature continuously the temperature must be logged at least once every working day. The equipment must have a “memory function” of temperatures (e.g. min/max temperatures are recorded) for holidays and the temperature must be logged the next working day.

In case of incorrect storage the monitor must be contacted without delay and the trial product must be set on-hold and not dispensed to subjects until notified by the monitor.

No trial product may be dispensed to any person except to the subjects enrolled into the trial.

Unused trial product must be stored separately from used trial product.

All trial products must be retained for inspection by the monitor after completion of the trial. The monitor will, upon completion of drug accountability, arrange for destruction of used, unused and broken vials of the supplied trial product.

### **9.4 Auxiliary supply**

All auxiliary supplies will be dispensed from the site facility.

## **10 Randomisation, breaking of blinded codes and interactive voice response system (IVRS)**

### **10.1 Randomisation and blinding**

The trial will be conducted as a randomised double-blinded trial, with a SD dose-escalation phase and a MD dose-escalation phase running in semi-parallel. After completion of the SD and MD dose-escalation phases, an MD expansion phase, at the maximum tolerated dose level, will be initiated. A MD dose cohort at a higher dose level than the SD dose cohort can not be initiated before the dose cohort in the SD phase has been completed.

Each clinical site will be supplied with boxes containing trial product. Each box of trial product will be labelled with a unique Dispensing Unit Number (DUN), the DUN of each individual vial contained in a box is identical to the box DUN. A subject can thus be allocated to more than one DUN per cohort he/she participates in.

At screening the subjects will be assigned the lowest available subject number, which will be used throughout the trial.

IVRS will allocate DUNs for the MD dose-escalation phase and the MD expansion phase.

In order to keep the trial site staff blinded, an unblinded, and otherwise trial-independent coordinator/pharmacist must be involved at each site in order to prepare the trial products and fill the syringes. Furthermore, a trial-independent nurse/site personnel must administer the trial product.

If subjects drop out before completion of trial Day 29 in the SD dose-escalation phase, and trial Day 57 in the MD phases, they must be replaced. Replacement should always occur to the same dose cohort as to which the subject who dropped out belonged. Randomisation lists will be provided by Clinical Supply Coordination.

### **10.2 Breaking of blinded codes**

The code for a particular subject may be broken in a medical emergency, if knowing the identity of the treatment allocation would influence the treatment of the subject. Whenever a code is broken, the person breaking the code must record the time, date and reason as well as his/her initials in the source documents. The subject should be withdrawn from the trial if the code is broken.

If the trial site needs to break the code, the sponsor should, if possible, be contacted prior to breaking the code. In all cases, the monitor must be notified within 24 hours after the code has been broken.

The treatment will be accessible for Investigator, Novo Nordisk Affiliate and International Product Safety, using IVRS for code breaking. The contingency plan for code breaking is using ClinPhone Support, available 24/7.

The central laboratory will not be provided with treatment reports. However, a copy of the treatment reports will be forwarded to the person responsible for bioanalysis of 109-0012 in DMPK & Bioanalysis, Novo Nordisk A/S, in order to facilitate the availability of intermediate PK results to be used for the safety evaluation during the trial. A copy of the the treatment reports will also be forwarded to the person responsible for PK/PD analysis in Biomodelling, Novo Nordisk A/S, in order to begin exploratory model development to assess the pharmacokinetic/pharmacodynamic properties of 109-0012.

### **10.3 Interactive voice response system (IVRS)**

For information about when to use IVRS, please see section [8](#).

## 11 Concomitant illnesses and medication

### Definitions:

Concomitant illness: any illness that is present at the start of the trial (i.e. at the first visit).

Concomitant medication: any medication other than the trial products that is taken during the trial, including the screening and run-in periods.

Details of all concomitant illnesses and medication must be recorded at trial entry (i.e. at the first visit). Any changes in concomitant medication must be recorded at each visit. If the change influences the subject's eligibility to continue in the trial, the sponsor must be informed.

The information collected for each concomitant medication includes, at a minimum, start date, stop date or continuing and indication.

## 12 Adverse events

### 12.1 Definitions

#### **Adverse event (AE):**

An AE is any undesirable medical event occurring to a subject in a clinical trial, whether or not related to the trial products.

Note: This includes events from the first trial related activity after the subject has signed the informed consent and until post-treatment follow-up period as defined in the protocol.

The following should not be recorded as AEs:

- Pre-planned procedure unless the condition for which the procedure was planned has worsened from the first trial related activity after the subject has signed the informed consent.
- Pre-existing conditions found as a result of screening procedures. These should be recorded as medical history/concomitant illness.

An AE can also be a clinical laboratory abnormality regarded as clinically significant i.e. an abnormality that suggests a disease and/or organ toxicity and is of a severity which requires active management (i.e. change of dose, discontinuation of trial product, more frequent follow-up or diagnostic investigation).

#### **Serious adverse event (SAE):**

An SAE is an experience that at any dose results in any of the following:

- Death
- A life-threatening\* experience
- In-patient hospitalisation\*\* or prolongation of existing hospitalisation
- A persistent or significant disability/incapacity
- A congenital anomaly/birth defect
- Important medical events that may not result in death, be life-threatening\*, or require hospitalisation\*\* may be considered an SAE when, based upon appropriate medical judgement, they may jeopardise the subject and may require medical or surgical intervention to prevent one of the outcomes listed in this definition

\* The term life-threatening in the definition of SAE refers to an event in which the subject was at risk of death at the time of the event. It does not refer to an event which hypothetically might have caused death if it was more severe.

\* \* The term hospitalisation describes a period of at least 24 hours. Over-night stay for observation, treatment at emergency room or treatment on an out-patient-basis does not constitute a hospitalisation. However, medical judgement must always be exercised, and when in doubt, the case should be considered serious. Hospitalisations for administrative, trial related and social purposes do not constitute hospitalisations as defined by the seriousness criteria for SAEs and should therefore not be reported as such. Likewise, hospital admissions for surgical procedures planned prior to trial inclusion are not considered adverse events.

#### **Non-serious adverse event:**

A non-serious AE is any AE which does not fulfil the definition of a serious AE.

#### **Relationship to trial product\* assessment definitions:**

The relationship of an adverse event should be assessed using the following categories:

- Probable: good reasons and sufficient documentation to assume a causal relationship
- Possible: a causal relationship is conceivable and cannot be dismissed
- Unlikely: the event is most likely related to an aetiology other than the trial product

\* Trial product is defined as Anti-IL-20 (109-0012) 100 mg/vial formulation or the corresponding placebo formulation.

#### **Outcome categories and definitions:**

- Recovered: fully recovered or by medical or surgical treatment the condition has returned to the level observed at the first trial related activity after the subject signed the informed consent
- Recovering: the condition is improving and the subject is expected to recover from the event. This term should only be used when the subject has completed the trial
- Recovered with sequelae: as a result of the AE, the subject suffered persistent and significant disability/incapacity (e.g. became blind, deaf, paralysed). Any AE recovered with sequelae should be rated as an SAE
- Not recovered
- Fatal
- Unknown: this term should only be used in cases where the subject is lost to follow up.

#### **Coding:**

All adverse events will be coded in MedDRA, current version.

### Severity assessment

The National Cancer Institute's (NCI) Common Terminology Criteria for Adverse Events (CTCAE) Version 3.0 will be used to assess and grade severity for adverse events and for laboratory abnormalities judged to be clinically significant.

The CTCAE Version 3.0 is a descriptive terminology with a grading (severity) scale provided for each AE term. Within each category, AEs are listed accompanied by their descriptions of severity (Grade 1-5). Each AE term will be mapped to a MedDRA term and code. For this trial the CTCAE will only be used for grading the severity of an AE and not for causality assessment.

If the event is not covered in CTCAE Version 3.0, the guidelines shown in [Table 12-1](#) should be used to assess severity.

**Table 12-1 Severity and toxicity grade of events not covered by CTCAE**

| Toxicity Grade/ Severity |                  | Description                                                                                                                                                                             |
|--------------------------|------------------|-----------------------------------------------------------------------------------------------------------------------------------------------------------------------------------------|
| Grade 1                  | Mild             | Transient or mild discomfort; no limitation in activity; no medical intervention or therapy required. The subject may be aware of the sign or symptom but tolerates it reasonably well. |
| Grade 2                  | Moderate         | Mild to moderate limitation in activity, no or minimal medical intervention/ therapy required.                                                                                          |
| Grade 3                  | Severe           | Marked limitation in activity, medical intervention/ therapy required, hospitalisations possible.                                                                                       |
| Grade 4                  | Life-threatening | The subject is at risk of death due to the adverse event as it occurred. This does not refer to an event that hypothetically might have caused death if it was more severe.             |
| Grade 5                  | Fatal            | The subject died due to the event.                                                                                                                                                      |

#### 12.1.1 Definition of dose limiting toxicities

Grade 3 AEs or higher will represent Dose Limiting Toxicities (DLT), except when the relationship to trial product is judged as unlikely.

#### 12.1.2 Definition of maximum tolerated dose and maximum administered dose

The maximum tolerated dose (MTD) is the highest dose level below the maximum administered dose (MAD) where none or 1 subjects experience a DLT.

The maximum administered dose is the highest dose given in the trial.

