### MD, expansion phase

The MD expansion phase will be initiated as long as there is an acceptable safety profile and an indication of efficacy. There will also be the possibility to go directly into a phase 2 dose-finding trial, and refrain from the MD expansion phase. The decision whether or not to continue with the MD expansion phase will be taken based on unblinded safety and efficacy data. Subjects included in the MD expansion phase will be treated at one single dose level of Anti-IL-20 (109-0012) 100 mg/vial, and in total 39 subjects will be included; 26 subjects will receive active trial drug and 13 subjects will receive placebo (N= 26+13). The selected dose level for the MD expansion phase will be the maximum tolerated dose, as observed from the SD and MD dose-escalation phases.

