## 5 Trial design

### 5.1 Type of trial

This is an adaptive, randomised, multicentre, double-blind, placebo-controlled phase 1/2a trial, studying the safety and tolerability of different dose levels of SD and MD of Anti-IL-20 (109-0012) 100 mg/vial. The trial will be performed in subjects with moderate to severe stable plaque psoriasis, with or without psoriatic arthritis. The MD dose-escalation will be performed partly in parallel with the SD dose-escalation phase; the first dosing of the MD dose-escalation phase will start when the third dose level of the SD dose-escalation phase has been evaluated by the Study Safety Group.

Initiation of the MD expansion phase, at the maximum tolerated dose, will depend on results from the dose-escalation phases and it will only be initiated as long as there is an acceptable safety profile. There will also be the possibility to go directly into a phase 2 dose-finding trial, and refrain from the MD expansion phase. The decision whether or not to continue with the MD expansion phase will be taken based on unblinded safety and efficacy data.

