### 5.3 Treatment of subjects

Anti-IL-20 (109-0012) 100 mg/vial or Placebo (109-0012) 0 mg/mL will be administered subcutaneously into the abdomen using a standard syringe. The active doses will range from 0.01 mg/kg to 3 mg/kg in the SD phase and from 0.05 mg/kg to 2 mg/kg in the MD phase. The maximum dose of 3 mg/kg has been chosen due to injection volume limitations. The dose to be investigated in the MD expansion phase will be the maximum tolerated dose reached in the previous phases and will not commence until the SD and MD dose-escalation phases have been

completed. For more details see [Table 5–1](#), which presents the anticipated dosing schedule for the different dose cohorts for the SD and MD dose-escalation phases.

The freeze dried drug product will be dissolved in Water for Injection at a concentration of 100 mg/mL and further diluted with the placebo formulation to 10 or 1 mg/mL for the lowest doses. The volume of each injection will not exceed 1.2 mL. The placebo formulation will be provided as a liquid formulation and will have an identical appearance as the reconstituted freeze dried active drug at the lowest doses. At the higher doses the reconstituted active drug solution might differ in colour due to high protein content.

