suggested half-life of about 15-20 days the drug is then anticipated to have been sufficiently cleared from the body.

Other anti-psoriatic treatments, except moisturising cream and low potency corticosteroid cream (group 1), will not be allowed during the trial. For more specific details regarding prohibited concomitant medication see section [6.3](#).

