| 1 of 4                                                                                   | Enter four subjects (3+1) at the same dose level as the current level where the toxicity event occurred.                                                                                                                                                                                                                                                                                                                                                                                                                                                                                                                        |
| 1 of 8                                                                                   | Enter four subjects (3+1) at the next dose level, according to Table 5–1 .                                                                                                                                                                                                                                                                                                                                                                                                                                                                                                                                      |
| ≥2                                                                                       | 
The dose-escalation will be stopped at this level, and no further increase of dose will occur. There will however be the possibility to add four (3+1) subjects at one or maximally two different dose levels between the current dose limiting level and the previous dose level.
 
 
• The maximum tolerated dose (MTD) is the highest dose level below the maximum administered dose (MAD) where none or 1 subjects experience a DLT.
 
• The maximum administered dose is the highest dose given in the trial.
 
• The maximal feasible dose is 3 mg/kg.
 
 |

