**Day 57 to Day 148 ( $\pm$  3 days)**

Subjects will come for regular visits at Day 57, 71, 99, 127 and 148. From Day 57 and onwards a deviation of  $\pm$  3 days from the scheduled day will be allowed. The following data and samples will be recorded and collected at each of those visits:

1. Vital signs
2. Haematology
3. Biochemistry
4. Urinalysis
5. Hormones
6. Sampling for serum/plasma biomarkers
7. PK samples
8. Concomitant medication

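### The MTD rule mixes single and repeated dosing: after a toxicity stop in the MD phase it can set the four-dose expansion at 1.5 mg/kg, a level planned only as a single dose

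*Protocol*

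**What the plan says.** Section 12.1.2 and Table 5-2 carry the same rule: "The maximum tolerated dose (MTD) is the highest dose level below the maximum administered dose (MAD) where none or 1 subjects experience a DLT". Section 12.1.2 continues: "The maximum administered dose is the highest dose given in the trial". Neither place says whether a level is a single or a repeated dose.

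The expansion dose follows from this MTD. Section 1 states: "The selected dose level for the MD expansion phase will be the maximum tolerated dose, as observed from the SD and MD dose-escalation phases". Section 5.3 says the same: "The dose to be investigated in the MD expansion phase will be the maximum tolerated dose reached in the previous phases". Under Section 5.1 the expansion uses the MD regimen of four doses, one every second week, in 39 subjects (26 active, 13 placebo).

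The planned ladders (Table 5-1) differ at the top:

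- SD: 0.01, 0.05, 0.20, 0.6, 1.5 and 3.0 mg/kg.
- MD: 0.05, 0.20, 0.5, 1.0 and 2.0 mg/kg.

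Two other provisions bear on the outcome. After a stop for 2 or more subjects with toxicity, Table 5-2 allows extra cohorts between the limiting level and the one before it: "There will however be the possibility to add four (3+1) subjects at one or maximally two different dose levels". Before the expansion there is an unblinded review (Section 5.1): "The decision whether or not to continue with the MD expansion phase will be taken based on unblinded safety and efficacy data".

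**The concern.** A single dose and four fortnightly doses of the same size are different exposures, so tolerance of the first does not establish tolerance of the second. The definition ranks both on one mg/kg scale. Once SD has gone higher than MD, the trial-wide MAD is an SD dose, and the highest qualifying level below it can also be an SD dose. The expansion would then repeat four times a level that was given only once, after repeated dosing had already caused dose-limiting toxicity.

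This is the only dose tested in the expansion. After an MD toxicity stop, the sponsor would either follow a rule that points too high or amend the protocol to use the tolerated MD level.

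**Working it through.** **Check of the dose scale.** Table 5-1 lists accumulated MD doses of 0.2, 0.8, 2.0, 4.0 and 8.0 mg/kg. These equal 4 × (0.05, 0.20, 0.5, 1.0, 2.0), so the table reproduces. Table 5-2 caps the feasible dose at 3 mg/kg, so in the MTD rule a dose means one administration, not the accumulated total.

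**Timing.** MD cohorts start at W15, W25, W35, W45 and W55 (Table 5-1). Escalation is decided on data through Day 57, about 8 weeks later; Section 8.1.2 schedules that visit ("Subjects will come for regular visits at Day 57, 71, 99, 127 and 148"). Read-outs therefore fall at about W23, W33, W43, W53 and W63. SD 3.0 opens at W25, before the read-outs of MD levels 2 to 5, so on the planned schedule the MAD is already 3.0 at those four read-outs.

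**Literal rule.** MAD = highest dose given in either phase. MTD = highest level below the MAD with 0 or 1 subjects with a DLT. Base case: SD has reached 3.0 (MAD = 3.0), SD 1.5 is tolerated, and no levels are added.

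| MD outcome | Literal expansion dose (mg/kg) | Highest tolerated MD dose (mg/kg) | Ratio |
|---|---|---|---|
| Stop at 2.0 | 1.5 | 1.0 | 1.5 |
| Stop at 1.0 | 1.5 | 0.5 | 3 |
| Stop at 0.5 | 1.5 | 0.20 | 7.5 |
| Stop at 0.20 | 1.5 | 0.05 | 30 |
| Completed, no stop | 2.0 | 2.0 | 1 |

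For stops at 1.0 or lower, the literal dose exceeds the dose that was stopped. The values are the same if SD 3.0 is itself dose-limiting. A stop at 0.05 is left out because its data arrive at about W23, before SD 3.0 opens. If SD escalation continued after such a stop, the rule would again return 1.5, with no tolerated MD level at all.

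**What changes the value.**

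- *Late DLTs at SD 1.5.* Escalation is decided at Day 15 but follow-up runs to Week 16. If the count at 1.5 later reaches 2 or more, the rule gives 0.6 for stops at 0.20, 0.5 or 1.0, and 1.0 for a stop at 2.0.
- *Added MD levels after a stop at 2.0.* If 1.5 or 1.75 is added and tolerated, the rule correctly returns that level. If 1.25 is tolerated and 1.75 is not, it returns 1.5 against a tolerated 1.25.
- *Added MD levels after a stop at 1.0 or lower.* They lie below the stopped level and cannot displace 1.5. With a stop at 1.0 and 0.75 tolerated, the rule gives 1.5, twice the tolerated dose.

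**Exposure.** Section 5.3 gives a "suggested half-life of about 15-20 days". Assuming simple exponential decay and ignoring absorption, the amount just after the fourth dose, relative to one dose, is the sum over k = 0 to 3 of 2^(−14k/t):

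- t = 15 days: 1 + 0.524 + 0.274 + 0.144 = 1.94.
- t = 20 days: 1 + 0.616 + 0.379 + 0.233 = 2.23.

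Four doses of 1.5 mg/kg therefore peak at the equivalent of 1.5 × 1.94 = 2.91 to 1.5 × 2.23 = 3.34 mg/kg, and total 6.0 mg/kg.

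**The case against.** The best counter-argument comes from Table 5-2 itself. The MTD text sits in the row for 2 or more toxicities, directly after a statement that escalation stops and the dose is not raised further. Read in place, the MTD belongs to the phase just stopped, and 1.5 mg/kg after an MD stop at 1.0 or lower would be a forbidden increase. That sentence governs escalation cohorts, however. It leaves the stop at 2.0 untouched, where 1.5 is not an increase. For lower stops it creates a conflict with the definition without naming the tolerated MD level as the answer. Reading MTD and MAD per phase contradicts the trial-wide MAD, and it fails in another case: if MD completes cleanly at 2.0, the MD-phase MAD is 2.0 and the MTD drops to 1.0.

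The exposure argument also has a limit. Where a single 3.0 mg/kg was tolerated, a peak of 2.9–3.3 is close to one already tolerated, although the total of 6.0 mg/kg is twice as large. By the same measure MD 1.0 peaks at 1.9–2.2, so a stop at 1.0, like the lower ones, is then less likely. None of this makes 1.5 a tolerated repeated dose once an MD level has been stopped for toxicity.

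Finally, the trigger is narrow, and the expansion requires an acceptable safety profile and the unblinded review. Those safeguards make it unlikely that subjects would actually receive such a dose. But the review decides only whether to proceed; no text lets it choose another dose.

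**Conclusion.** The concern holds: the stated rule gives a wrong expansion dose after an MD toxicity stop. With SD at 3.0, SD 1.5 tolerated and planned levels only, it returns 1.5 mg/kg for MD stops at 0.20, 0.5, 1.0 and 2.0. The most relevant cases are 1.5 times the tolerated MD dose (stop at 2.0) and 3 times (stop at 1.0). The rule works if MD completes, or if a tolerated MD level of 1.5 or above is added after a stop at 2.0. How often the failing cases would arise cannot be derived from the protocol. This should be fixed before the expansion dose is chosen; the likely practical cost of leaving it is an amendment made after a toxicity stop.

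**What to change.** Replace the definition in Section 12.1.2 and Table 5-2 with:

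> The MTD is determined separately for the SD and MD phases. In each phase it is the highest level given in that phase (including the top level and any intermediate level added) at which it and all lower levels in that phase have none or 1 subject with a DLT. If the stopping count (2 or more) is never met, the highest level given is reported as tolerated and the MTD as not reached. The expansion dose is the MD-phase value (the MTD, or the highest tolerated level if the MTD is not reached). If no MD level qualifies, the expansion phase is not started.

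Align the expansion-dose sentences in Sections 1, 5.1 and 5.3. On planned levels, MD stops at 0.20, 0.5, 1.0 and 2.0 and a completed MD phase then return 0.05, 0.20, 0.5, 1.0 and 2.0 mg/kg respectively. The change is wording only.
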